**Quantitative phases**

**Phase 1: Cross-sectional study**

**The type of study:** We will conduct a descriptive and analytical cross-sectional study.

**Study population:** Community-dwelling single-living older adults and registered with Iranian national government Electronic Health Records (EHRs) at Gorgan Health Center, North-east of Iran, will be recruited.

**The method of collecting information**

A total of two-hundred and twenty-two community-dwelling lonely older people covered by Gorgan health care-centers with inclusion criteria will be recruited, based on census sampling method. The research team will make contact to community-dwelling older adults (aged ≥ 60 years) registered as lonely persons in the health records in the Health Center of Gorgan city, Iran and explain the purpose of conducting the survey and, invite them to participate in the project. The researcher will suggest an appropriate time and date for a face-to face visit at a day care center (Kanon Salmandi Jahan-Didegan) in Gorgan city, where the questionnaires will be completed under the rules of Covid-19 health protocols (following social distancing of at least two meters, wearing a mask).

**Measures**

**Socio-demographic characteristics and health conditions**

Socio-demographic characteristics will be assessed using the following 13 items: age, gender, level of education (illiterate, primary education, secondary education and tertiary education), income (Iranian currency), employment condition (employer, pensioner (somebody who receives a steady salary after her retired husband or father’s death) , retired person (an older person who receives a steady salary after finishing his/her own work activity ), and homemaker, and others, number of children, living neighborhood (residency) of offspring(s) ( 15-45 minute buffer zone distance between offspring (s) and older parents), health condition (disability, chronic disease (yes/no), participation in social and religious activities (yes/no), social distress (family conflict (yes/ no), death of close family member and/or friend in the last 6 months (yes/ no), sleep quality (good/ bad ), being a daily smoker (yes/no).

**Questionnaires**

**Loneliness** will be assessed using the Persian version(45), of the 20-item UCLA Loneliness Scale (UCLA -20, Version 3). The range score for this scale is 20-80, and a higher score indicates a more intense level of feeling of loneliness(46). Cronbach's alpha coefficient of this questionnaire among Iranian older adults is reported to be 0.81 (45).

**Quality of life** will be determined using the 19-item Control, Autonomy, Pleasure and Self-realization (CASP-19). The minimum score of the questionnaire is 0 and the maximum score is 57 (47). Its internal consistency in the Persian version among Iranian older adults was 0.97 (48).

**General health** will be evaluated using 12 item General Health Questionnaire (GHQ12). The total scores ranges from 0 to 36, where higher scores indicate higher level of mental distress(49). The reliability and validity of this questionnaire among Iranian older adults has been conducted Namjoo and et.al (50).

**Social support** will be appraised using the 12 item Multidimensional Scale of Perceived Social Support (MSPSS); possible scores range from 12 to 60. Perceived Social Support scoring comprising low (12-20), moderate (20-40), and high (40+)(51). The Cronbach's coefficient alpha value among Iranian older adults was 0.73 (52)

**Self-care ability** will be measured using 17-item Self-care Ability Scale for the Elderly (SASE). The minimum score of the questionnaire is 17 and the maximum score is 85(53). Its internal consistency in the Persian version among Iranian older adults was 0.73 (54).

**Social network** will be assessed using Lubben Support Network Scale-6 (LSNS-6). Total scores is ranged from 0 (low level of social support) to 30 (high level of social support)(55). The Cronbach's coefficient alpha among Iranian older people was 0.77(56).

Moreover, three open-ended questions will be asked to identify support services required at home as well as all the problems related to living alone:

1. What are the challenges with living alone?
2. What services (Personal /Practical) do you need at home?
3. What skills and/or abilities do you have to help your peers? (For both givers and receivers).

**Statistical analysis**

Data analysis will be conducted using IBM SPSS v26 software. Mean and standard deviation will be reported for continues normally distributed data and interquartile range and median for data deviating from normal distribution. Results of the categorical variables will be presented as percentage and frequency. Independent t-test will be used to determine whether there will be a difference in the feeling of loneliness scores and categorical variables. A chi-square test will be employed to assess a significant association between categorical variables. Regression analysis will be undertaken to explore the relationship between socio-demographic variables and feeling of loneliness. Multiple logistic analysis regression analysis will be conduct to control potential confounding variables including: age, gender, level of education, ethnic, income, and job.

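### Phase 1 names a two-group t-test for variables with four and five levels, and a logistic model where the implied outcome is a 20-80 score with no cut-off

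*Protocol*

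**What the plan says.** The Phase 1 Statistical analysis section of the Protocol contains three statements that matter here.

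- Group comparisons: "Independent t-test will be used to determine whether there will be a difference in the feeling of loneliness scores and categorical variables". The statement is not restricted to two-level variables, and Phase 1 names no ANOVA or Kruskal-Wallis test.
- Regression, type not given: "Regression analysis will be undertaken to explore the relationship between socio-demographic variables and feeling of loneliness".
- Adjusted analysis: "Multiple logistic analysis regression analysis will be conduct to control potential confounding variables including: age, gender, level of education, ethnic, income, and job". No dependent variable is named.

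The variables are defined earlier. Under Questionnaires, the loneliness scale is described thus: "The range score for this scale is 20-80, and a higher score indicates a more intense level of feeling of loneliness". No cut-off or lonely/not-lonely category for it appears anywhere in the Protocol. The same section does give low, moderate and high bands for the social support scale.

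Under Socio-demographic characteristics and health conditions, education has four levels: "level of education (illiterate, primary education, secondary education and tertiary education". Employment opens with "employment condition (employer, pensioner (somebody who receives a steady salary after her retired husband or father’s death" and goes on to retired, homemaker and others, which makes five. Several other items are binary, for example "sleep quality (good/ bad ), being a daily smoker (yes/no".

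**The concern.** A two-group t-test compares two means. One such test cannot assess a variable with four or five levels. An analyst following the text would have to run several pairwise tests, merge categories, or depart from the stated method, and the Protocol does not say which.

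A binary logistic model needs a two-valued outcome. If the outcome is loneliness, as the preceding sentence suggests, the only variable defined is a score, so the model cannot be fitted until someone chooses a threshold.

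At stake are the error rate of the education and employment comparisons and the precision of the only confounder-adjusted analysis named for Phase 1. The sample is a census of fixed size, so lost information cannot be recovered by recruiting more people.

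**Working it through.** The Protocol states no alpha, power or effect size for Phase 1, so there is no figure of its own to reproduce. The check is whether each named method fits its variable, followed by the size of the consequences under stated assumptions.

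**Inputs from the Protocol.** Phase 1 sample 222 (The method of collecting information); education 4 levels, employment 5 (Socio-demographic characteristics and health conditions); loneliness score 20 to 80 (Questionnaires).

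**Assumptions.** Two-sided alpha 0.05; normally distributed scores with equal variance.

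**1. Pairwise t-tests.** The number of pairs is k(k-1)/2.

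- Education: 4 × 3 / 2 = 6 pairs.
- Employment: 5 × 4 / 2 = 10 pairs.

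With equal groups and large samples, the chance of at least one false positive is the probability that the studentized range of k means exceeds 1.96 × √2 = 2.77.

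- k = 4: 0.203
- k = 5: 0.286

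Simulation under the null with 222 normal scores (4,000 runs per setting, equal and unequal group sizes) agrees:

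| Variable | Any pairwise t-test significant | One-way ANOVA significant |
|---|---|---|
| 4 levels | 0.188 to 0.192 | 0.048 to 0.050 |
| 5 levels | 0.282 to 0.286 | 0.046 to 0.049 |

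Treating the tests as independent would overstate the rates: 1 - 0.95^6 = 0.265 and 1 - 0.95^10 = 0.401. The pairs share groups, so the lower figures apply.

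**2. Splitting the score.** The share of information kept when a normal score is cut so that a proportion p lies on one side, at normal quantile z, is φ(z)² / [p(1 - p)].

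| Split | Kept | Lost | 222 people act like |
|---|---|---|---|
| Median (p = 1/2) | 0.637 | 36% | about 141 |
| Top third (p = 1/3) | 0.595 | 41% | about 132 |
| 20/80 (p = 0.2) | 0.490 | 51% | about 109 |

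A linear model of the score avoids this loss. The Protocol gives no cut-off, so these splits are illustrations. The more uneven the split, the greater the loss.

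**The case against.** The strongest reply is that this is incomplete drafting rather than error. The logistic sentence names no outcome. The unspecified regression in the sentence before it may already be linear, and a cut-off could be set in a statistical analysis plan that is not shown. The Protocol never says that pairwise t-tests will be run. Phase 1 is an exploratory survey.

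Much of this is fair and limits the point. It does not remove it: the Protocol names particular methods, and as named they do not fit the variables it defines. That differs from leaving a detail to a later document.

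A reader might infer more than the text supports:

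- *That logistic regression will be applied to the raw score, or that a cut-off will be picked after seeing the data.* The Protocol says neither. That loneliness is the outcome is an inference from the preceding sentence, and the timing of any cut-off is simply not stated.
- *That error rates of 20% and 29% are built into the plan.* They arise only if all pairs are tested without correction. An overall test, or two-level groupings fixed beforehand, would avoid them.
- *That the logistic model would have too few events for its covariates.* This cannot be established. The one-third prevalence in the Introduction describes older people in general, while Phase 1 recruits people recorded as lonely. The Protocol gives neither the proportion above any threshold nor the coding of the covariates.
- *That none of the Phase 1 tests fit.* The t-test suits gender and the yes/no or good/bad items, and the chi-square test suits associations between categorical variables.

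**Conclusion.** The point holds for two parts of the Phase 1 analysis. First, the independent t-test cannot test education or employment, and nothing else is named for them. Uncorrected testing of all pairs, if done, would give a false-positive rate of about 20% and 29% per variable, against about 5% with ANOVA. Second, the adjusted model is named as logistic although its implied outcome is defined only as a score. Splitting that score at the median or the top third would discard about 36% to 41% of the information from 222 people.

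The sizes rest on an alpha of 0.05, normal scores and illustrative cut-points, none of which the Protocol gives for Phase 1. The mismatch between method and variable does not depend on them, although its logistic part does depend on reading loneliness as the outcome. The issue is confined to the survey: the Phase 2 comparison has its own stated methods and is untouched. The wording should be corrected before the Phase 1 data are analysed.

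**What to change.** Reword the Phase 1 Statistical analysis section in two places.

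1. Keep the independent t-test for two-level variables. Name one-way ANOVA, or Kruskal-Wallis where scores are not normal, for variables with three or more levels such as education and employment.
2. Name the adjusted analysis as multiple linear regression of the continuous UCLA-20 score on the covariates already listed. If logistic regression is kept as a secondary analysis, state its outcome and a justified cut-off in advance.

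The cost is wording only. No further participants, data or software are needed.

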**Phase 2: intervention program**

**Type of the study:** This is a quasi-experimental study, pre-post intervention, with control group.

**Sample size:** Following the cross-sectional baseline assessment, a sample of thirty-two lonely older adults who meet the inclusion criteria will be recruited to the intervention program. The sample size was calculated using the following formula:

[figure not shown]

With 95% confidence interval and 80% power(57). The sample size is calculated to be 27. Considering a potential attrition rate of 15%, the final sample size is calculated to be 32.

**The method of collecting information**

Then, participants in the intervention group will be invited for an information session held at the day care center, during which all details related to intervention program will be explained. This session will provide an opportunity for intervention group to get to know each other. Participants willing to join the study will have to complete a written informed consent form. Participants will receive informal home care support intervention for loneliness (HoSIP) program through mutual peer support for approximately 12 weeks (3 months).

The participants in the control group with similar characteristic to those of intervention group will be selected from one of the cities of Golestan province, Aliabad-e- Katul, which is 42 Km away from Gorgan city, with an area of 1163 square kilometers. It is the third largest city of Golestan province (Gorgan, Gonbad-Kabus, and Aliabad-e-Katul). Aliabad-e-Katul has similar cultural characrtistics to Gorgan city for instance, different ethnicities such as Fars, Sistani, Kurd, Turk, and Shahrodi all living in both cities (58). Due to ethical consideration, the control group will receive the same intervention program at the end of the study.

The HoSIP program will provide lonely older adults with informal home care services in the form of scheduled daily activities through an online social networking platform and face-to-face meetings during 12 weeks (3 months). After selecting the participants for the intervention group, the subjects will be registered in an online social network (whatsapp) named "HAMDAM". The participants will be able to express their daily needs such as emotional (e.g. empathy, encouragement), informational (knowledge translation), instrumental (e.g. cooking, shopping), and affiliational (making social relationship between lonely older adults, reinforcing the sense of belonging) supports in the HAMDAM social network consequently, a peer volunteer (lonely older adult) in the HAMDAM social network will provide the desired service for lonely older adults in need of service. In this procedure, all lonely older adults can provide services to any of their peers. For example, if a lonely older adult declares a need in the HAMDAM social network, any member of the group who could meet his/her need can get involved in the informal service delivery. All informal home care services will be carried out in as face-to-face meetings at the daycare center and/or online sessions. These activities will be carried out under the supervision of the first researcher and two project partners. The researcher and two project partners will monitor all activities (both face-face meetings and online sessions) and will be facilitators during 12 weeks (3 months) intervention program**.**

The phone number of the researcher and two project partners will be given to those older adults who would like to participate in the intervention program but with no online availability. If these lonely older adults need a specific service, they will contact the research team which will see to that a peer volunteer in the network will be contacted by the research team to support the person in need of service. All services will be free of cost and lonely older adults will benefit from mutual support from one to the other in the HAMDAM social network. In the online social network, numerous educational information on healthy aging such as coping with retirement stress, healthy nutrition, self-care, and meaningful activities, will be delivered by the research team once per day to inform lonely older adults about health issues in aging.

**Phase 3: Qualitative evaluations**

**This phase will be conducted in two stages**

**Stage 1:**

post-test will be conducted at three points (immediately after intervention, three months and six months after intervention). All questionnaires (UCLA-20; CAPS-19; GHQ-12; MSPSS-12; LSNS-6; SASE-17) will be completed among intervention group and control group.

**Statistical analysis**

Analysis of variance with repeated measures will be used to compare outcome measures baseline, post-intervention and follow-up assessments. Paired t-test and covariance analysis will be used to assess the impact of the intervention by adjusting basic comparison and socio-demographic variables in cross-sectional study.

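### The protocol assigns a within-group paired t-test, beside covariance analysis, to the intervention's impact and names no between-group or group-by-time contrast as the effect

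*Protocol*

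**What the plan says.** The Phase 2 section sets the design: "This is a quasi-experimental study, pre-post intervention, with control group". On the controls, it says: "The participants in the control group with similar characteristic to those of intervention group will be selected from one of the cities of Golestan province". They are therefore not randomised and live in a different city.

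Phase 3, Stage 1 sets the timing: "post-test will be conducted at three points (immediately after intervention, three months and six months after intervention". All six questionnaires "will be completed among intervention group and control group". Control data thus exist at every post-test.

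The Statistical analysis paragraph that follows has two sentences. The first is "Analysis of variance with repeated measures will be used to compare outcome measures baseline, post-intervention and follow-up assessments". The second gives the methods for the effect: "Paired t-test and covariance analysis will be used to assess the impact of the intervention by adjusting basic comparison and socio-demographic variables". Neither mentions group as a factor, a group-by-time term or a difference between groups. Neither says which of the three methods decides.

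**The concern.** A paired t-test uses one group's own before and after scores and makes no use of the controls. Here it is assigned to the impact of the intervention and is not presented as a description of change. The repeated-measures ANOVA sentence does not supply the missing contrast, because as worded it compares time points.

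The controls were added so that change under the programme could be set against change without it. Some common change is plausible. The Phase 1 survey runs under COVID-19 distancing and mask rules, and follow-up extends to six months after a 12-week programme. If loneliness or distress moves in both cities over that time, the paired test credits the movement to the programme. If the paired test and the covariance analysis disagree, the text allows either to be reported as the impact.

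**Working it through.** **Inputs from the protocol.** Before attrition the sample size is 27, "With 95% confidence interval and 80% power(57". I take this as two-sided alpha 0.05. There are four assessments: baseline and three post-tests. The attrition statement is "Considering a potential attrition rate of 15%, the final sample size is calculated to be 32". It reproduces: 27 / 0.85 = 31.8, rounded up to 32. The 27 cannot be rebuilt, because the formula is a figure that is not shown and the text prints no effect size or SD. The text also does not say whether 27 is per group or in total.

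**Assumptions.** No true effect. Both groups drift by the same amount d, in units of the outcome SD. The pre-post correlation r is 0.5 to 0.7. The protocol gives none of these values.

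**Paired t-test in the intervention group.**

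- SD of change = √(2(1 − r)): 1.000 at r = 0.5 and 0.775 at r = 0.7.
- Noncentrality = d / √(2(1 − r)) × √27. For d = 0.3 this is 0.3 × 5.196 = 1.56 at r = 0.5, and 0.387 × 5.196 = 2.01 at r = 0.7.
- The chance of a significant result comes from the noncentral t distribution with 26 degrees of freedom.

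| Shared drift | r = 0.5 | r = 0.6 | r = 0.7 |
|---|---|---|---|
| 0.3 SD | 32.4% | 38.9% | 49.1% |
| 0.5 SD | 70.6% | 79.8% | 89.8% |

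If the planned total is split between two groups, the rates fall but stay well above 5%. With 16 in the group they are 20% to 31% at 0.3 SD and 47% to 68% at 0.5 SD. With 13 they are 17% to 25% and 38% to 57%. Each range runs from r = 0.5 to r = 0.7.

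**Comparison of methods under the same drift.** Simulation of 4,000 trials with 27 per group, four visits, r = 0.5, equal baseline means and no true effect:

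| Analysis | No drift | 0.3 SD | 0.5 SD |
|---|---|---|---|
| Paired t-test, intervention group | 5.4% | 31.5% | 70.1% |
| Repeated-measures ANOVA, time effect within one group | 5.1% | 30.2% | 73.8% |
| Repeated-measures ANOVA, group-by-time | 5.2% | 4.8% | 5.1% |
| Covariance analysis with group and baseline score | 4.9% | 4.9% | 5.1% |

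The two analyses that use the control group hold their error rate, and the two within-group analyses do not. The simulation covers drift common to both cities. It does not cover drift that differs between them.

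**The case against.** The strongest reply is that the sentence also names covariance analysis and speaks of adjustment. A paired t-test takes no covariates, so the adjusted assessment can only be the covariance analysis. With controls measured at every visit, group is its natural factor. This stands: a sound method is already in the plan. But group is not written into it, and the paired test is given the same task with no order of precedence.

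A reader might infer that the effect will be judged by within-group methods alone, or that the repeated-measures ANOVA will read any trend as effect. The text supports neither. The first inference overlooks the covariance analysis. The second holds only for a time effect, and the text neither specifies nor excludes a group-by-time term.

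A reader might also infer that anyone who misses one visit is dropped. The protocol states no deletion rule. Such loss belongs to classical repeated-measures ANOVA. A paired test or a single covariance analysis loses only those missing one of the two visits compared. Missing-data rules may sit in a SAP that is not shown, and the attrition was budgeted: 32 × 0.85 = 27.2, against 27 needed.

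Two further points limit the concern. Regression to the mean is possible but not established: people are recruited from those registered as lonely, yet eligibility sets no loneliness-score threshold. The protocol also frames part of the work as feasibility, with a preliminary look at participant responses. That lowers the weight any one test should carry. It does not make a within-group test a measure of impact.

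**Conclusion.** Wrong as written, within limits. The defect is a misassigned test together with an effect never defined as a contrast between groups. It is more than detail left to a SAP, because the protocol itself gives the paired test this purpose.

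With 27 participants and no true effect, the paired test would be significant in about 32% to 49% of trials under a shared drift of 0.3 SD, and in about 71% to 90% under 0.5 SD. A between-group analysis of the same data stays near 5%. The figures rest on the assumed drift and correlation, and they describe the conclusion only where the paired test is taken as the answer. They do not show that a drift will occur, or that the planned covariance analysis is faulty.

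**What to change.** In the Statistical analysis paragraph of Phase 3, Stage 1, state the following:

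- The intervention effect is the between-group difference at each post-test, adjusted for the baseline score and the planned socio-demographic variables. It comes from the covariance analysis already named, with group as the factor. An equivalent mixed model with group-by-visit terms that uses all observed post-tests would also serve.
- If repeated-measures ANOVA is kept, its group-by-time term is the test of effect.
- Paired t-tests are reported only as descriptive within-group change.

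The socio-demographic adjustment should stay, because the controls come from another city. The cost is protocol wording only, with no new data. The change does not remove confounding from the non-randomised control city, and a drift that differs between the two cities would still look like an effect.

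### Ethnicity is a named confounder in the Phase 1 model but no item collects it, and no stated step obtains the Phase 2 socio-demographic covariates from the controls

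*Protocol*

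**What the plan says.** **Phase 1 (cross-sectional survey).** The population is people "registered with Iranian national government Electronic Health Records (EHRs) at Gorgan Health Center". The collection section gives 222 "community-dwelling lonely older people covered by Gorgan health care-centers with inclusion criteria will be recruited, based on census sampling method". The form is introduced with "Socio-demographic characteristics will be assessed using the following 13 items: age, gender, level of education", followed by the rest of the list. The Phase 1 Statistical analysis section then uses multiple logistic regression to "control potential confounding variables including: age, gender, level of education, ethnic, income, and job".

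**Phase 2 (intervention with control group).** The design is quasi-experimental. The intervention group is recruited after the Gorgan survey. The controls "will be selected from one of the cities of Golestan province, Aliabad-e- Katul, which is 42 Km away from Gorgan city". They are described as "The participants in the control group with similar characteristic to those of intervention group", with no matching variables named. As an example of the cultural similarity of the two cities, the protocol mentions "different ethnicities such as Fars, Sistani, Kurd, Turk, and Shahrodi all living in both cities".

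**Analysis of the intervention effect.** The Statistical analysis section under Phase 3, Stage 1 specifies repeated-measures analysis of variance, and a paired t-test and covariance analysis "adjusting basic comparison and socio-demographic variables in cross-sectional study". The Method/design section says that a pretest takes place at baseline but does not say what the controls complete at it.

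**The concern.** An analysis can adjust only for what was recorded, on everyone who enters the model. The protocol falls short of this in two places.

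First, the Phase 1 model names a confounder that its own form does not ask about. Whoever runs the analysis must drop ethnicity without a plan for doing so, or look for it afterwards.

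Second, the protocol's only socio-demographic form belongs to a survey that the controls are not in. City and treatment coincide completely, so differences between the cities in age, education, income or employment would mix with the effect of the programme. Covariate adjustment is the main analytic means the protocol offers against that, and it needs the same variables from both groups. If the controls' form is forgotten, the adjusted comparison cannot be made as planned. Income and employment at baseline are hard to recover reliably months later, and no later analysis plan can supply data that were not collected.

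**Working it through.** No effect size or power calculation bears on this point. The check sets the named covariates against the form, and the form against the people who receive it.

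**Step 1: the plan's own count of 13 items.** Taking health condition as one item and the two social-distress questions separately, the list is: age, gender, education, income, employment, number of children, residence of offspring, health condition, social and religious participation, family conflict, recent bereavement, sleep quality, daily smoking. That makes 13, as stated. Splitting health condition into disability and chronic disease gives 13 + 1 = 14. Keeping it as one and merging the two social-distress questions gives 13 − 1 = 12. Ethnicity is absent on every count.

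**Step 2: confounders named for the Phase 1 model, against the form.**

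| Named confounder | On the form? |
|---|---|
| Age | Yes |
| Gender | Yes |
| Level of education | Yes |
| Ethnicity | No |
| Income | Yes |
| Job | Yes (employment condition) |

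Five of six are available and 6 − 5 = 1 is not. The three open-ended questions and the six scales do not ask about ethnicity either. The health records are described as the means of identifying and contacting people, and the protocol takes no covariate from them. The gap therefore applies to all 222 planned participants.

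**Step 3: who completes the form, against who enters the Phase 2 model.**

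- Survey population: Gorgan registrants, seen at a day care center in Gorgan.
- Intervention group: recruited after that survey, so their covariates are on file.
- Control group: Aliabad-e-Katul, 42 km away, and outside the survey.
- Socio-demographic form given to the controls: no section says so.
- Baseline pretest: stated for the controlled study, contents for the controls not stated.
- Six scales in both groups: stated under Phase 3, Stage 1, for the post-test visits. Fixed characteristics would not be asked again at those visits, so the form's absence there says nothing about baseline.

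**Step 4: the two readings of the adjustment sentence.** If the cross-sectional study is the source of the data, the covariates exist for the intervention arm only. If it only identifies the list of variables, the model is well defined, but it still needs a step in which the controls supply them. Neither reading provides that step.

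**The case against.** The strongest reply concerns Phase 2. The adjustment sentence may simply point back to the protocol's only list of socio-demographic variables. A pretest is planned, and choosing controls who resemble the intervention group requires knowing something about them. Nothing says their characteristics will not be recorded. This stands, and it rules out several stronger conclusions that a reader might draw:

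- *That every control will lack covariates, or that the Phase 2 model cannot be fitted.* The text shows an unstated collection step, not a decision to omit the data. A comparison adjusted for baseline score does not depend on the form at all.
- *That adjustment for these covariates is the only protection against confounding.* Selection of similar controls and use of pretest scores are also intended.
- *That ethnicity is a missing covariate in both Phase 2 groups.* It is named only in the Phase 1 model. In Phase 2 it appears as a description of the two cities, not as a variable in the effect model.
- *That the two groups' baselines differ in date or setting.* The intervention group is recruited after the survey, but no date or place is given for the controls' pretest. A gap is possible and not shown.

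The reply does not reach the Phase 1 mismatch, which needs no interpretation. Nor does it supply the missing step for the controls. What is asked, and of whom, is for the protocol to fix and cannot be left to a separate analysis plan.

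**Conclusion.** The point holds in two parts of different strength.

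**Phase 1: a definite contradiction.** One of six named confounders has no data item, for all 222 planned participants. The logistic model cannot be fitted as stated, although a model with the other five can. This assumes that the form, the open questions and the scales are the only data sources, as the protocol describes them.

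**Phase 2: a real gap in the collection plan.** None of the socio-demographic covariates has a stated collection step for the control group. Only on the literal reading of the adjustment sentence are they confined to one arm. How much data would be lost cannot be put as a number, because the protocol does not say what the controls complete at pretest. The gap matters because allocation is by city and not random.

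Both parts should be settled before data collection, since they are cheap to correct then and hard to repair afterwards.

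**What to change.** 1. Add an ethnicity item to the socio-demographic form, for example with the five groups the protocol already names plus an other category. If ethnicity will not be collected, delete it from the confounders of the Phase 1 model.
2. State in the Phase 2 collection section that the controls complete the socio-demographic form and all six scales at the baseline pretest.
3. Reword the Phase 3, Stage 1 analysis sentence along these lines: *adjusting for baseline score and socio-demographic variables measured at pretest in both groups*.

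The cost is one extra item for the Gorgan participants and one short form for the controls. Repeating the scales in the 32 people to be recruited to the programme is needed only if the survey does not fall close to its start. The protocol should say which is the case.
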